#### Secondary

Women who receive iCBT +TAU compared to those receiving only TAU willreport a higher quality of life, better coping strategies, a more functional parent-child bonding, and a higher marital/partner satisfaction.have fewer re-visits to the clinic and counselling appointments.become pregnant and have vaginal births to a greater extent than the women receiving only TAU.

In addition, during the study period, a health economic evaluation will be performed and the preliminary effects of partner support will be investigated.

### Participants

Participants will be recruited at four hospitals in Sweden: Uppsala University hospital with 4000 annual births; Örebro University hospital with 2700 annual births; Linköping University with 2800 annual births, and Falun regional hospital with 3000 annual births.

Women, aged ≥18 years with a negative birth experience and/or an immediate caesarean section and/or a major postpartum haemorrhage are eligible. Exclusion criteria are severe mental illness, stillbirth, neonatal death, ongoing CBT treatment, difficulties understanding Swedish and women who are unable to use the Internet on a computer.

### Sample size and power

There was a lack of studies for power calculation regarding iCBT for this population at the planning stage of this study. We therefore used information from a study that investigated iCBT for PTSD (due to other events) in a Swedish context [45]. This study had a large effect size on the continuous primary outcome measure (*d* = 1.25) in favour of the treatment group. We estimated a conservative medium effect size (Cohen’s *d* = 0.5), *α* = .05, and a power of 0.8 based on this study. A total sample size of 130 participants is needed for between-subjects t-test contrasts. For categorical outcome measures, a medium effect size (*ω* = 0.3), *α* = .05, df = 1, and a power of 0.8 was used to calculate the needed sample size. A total sample size of 88 participants is needed for *χ*^2^ analysis.

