### Posttraumatic stress following childbirth

In a meta-analysis, the prevalence for PTSD following childbirth (PTSD FC) was 3.1% among community samples and 15.7% among high-risk samples (e.g. pregnancy complications, emergency caesarean section, preterm birth) [6]. In a more recent review [7], the estimated prevalence was 2.4% among community samples, and 4.9% including both community plus high-risk samples when controlling for previous PTSD. The prevalence for clinically significant post-traumatic stress symptoms ranged between 9.6 and 27.3% [7]. The variation in prevalence rates may be explained by the timing and method used for assessment of PTSD criteria and symptoms [6, 7]. Prevalence rates were consistently higher in both studies when assessed close to childbirth. The prevalence rates above are based on the fourth edition of the Diagnostic and Statistical Manual for Mental Disorders (DSM-IV-TR) [8]. There is no sub-clinical or partial PTSD diagnose in DSM-IV, which is reflected in the heterogeneity regarding definition and label of clinically significant post-traumatic stress symptoms.

The definition of stressors for the development of PTSD according to DSM-IV can be applied to posttraumatic stress FC. A diagnosis of PTSD required affirming the following criteria: the stressor criterion (A) included stressful situations in which a person experience, witness, or is confronted with an event that involves actual death or threat of death or serious injury, or a threat to the physical integrity of self or others; the three symptom criteria re-experiencing (B), avoidance (C), and increased arousal (D); the duration criterion (E), and the influence criterion (F). Several risk factors are associated with PTSD FC, such as psychological factors (e.g. fear of childbirth), prepartum and partum factors (e.g. type of delivery) and postpartum factors (e.g. poor coping) [6, 9]. In a systematic review, five categories of risk factors for PTSD FC are identified: negative perception of childbirth, maternal mental health, history of trauma and PTSD, delivery mode and complications, and low social support [7].

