### Hypothesis

#### Primary

Women who report a negative experience from childbirth and receive iCBT+TAU will report lower levels of posttraumatic stress and depressive symptoms, as well as a smaller proportion of participants classified as fulfilling the criteria for PTSD, and a smaller proportion of participants with postpartum depression according to cut-off compared with those receiving only TAU.

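### The 88 women for the binary primary outcomes follow from w = 0.3, but no stated proportions support that effect and it does not fit the plan's own d = 0.5 on the same instruments

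*Protocol article*

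**What the plan says.** The primary hypothesis (Hypothesis, Primary) covers the symptom levels and also two binary outcomes: "a smaller proportion of participants classified as fulfilling the criteria for PTSD, and a smaller proportion of participants with postpartum depression according to cut-off". Under Primary outcome measures, PTSD is classified from the Traumatic Event Scale (TES) and depression from the Edinburgh Postnatal Depression Scale (EPDS) at 12 or more. The summed scores of the same two scales are compared as means.

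Sample size and power treats the two kinds of outcome separately:

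- Continuous: "We estimated a conservative medium effect size (Cohen’s *d* = 0.5), *α* = .05, and a power of 0.8", leading to "A total sample size of 130 participants is needed for between-subjects t-test contrasts".
- Binary: "a medium effect size (*ω* = 0.3), *α* = .05, df = 1, and a power of 0.8", leading to "A total sample size of 88 participants is needed for" the χ² analysis.

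No TAU or iCBT proportion is given for either binary outcome, and w is not linked to d. The Background cites PTSD prevalences of "3.1% among community samples and 15.7% among high-risk samples" from a meta-analysis. A later review gives 2.4% (community) and 4.9% (community plus high-risk). No prevalence of EPDS ≥ 12 is given.

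**The concern.** The binary outcomes are classifications taken from the scales whose means are compared. Cutting a scale normally discards information, so one would expect the proportions to need more women than the means. The plan has them needing about a third fewer (88 against 130). Both effects carry the label medium, but they do not describe the same treatment effect.

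Two components of the primary hypothesis are therefore presented as adequately powered on an assumption that the rest of the paragraph does not support. A reader who accepts it may take a non-significant difference in PTSD or depression proportions as evidence of no effect, when the trial had limited power to detect the effect it planned for.

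**Working it through.** **1. The plan's own figures.**
- Binary: N = (1.960 + 0.842)² / w² = 7.849 / 0.09 = 87.2, so 88. Noncentral χ² power (df 1) at 88 is 0.804. The figure reproduces.
- Continuous: a two-sided t-test with d = 0.5 needs 63.8 per arm, so 128 in total; 65 per arm gives power 0.808. The 130 reproduces closely.

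**2. What d = 0.5 implies for w.** Assumption: a normal score with equal SD in both arms, shifted by d and cut at one point, with 1:1 allocation. Then
- p₂ = Φ(Φ⁻¹(p₁) − d)
- w = |p₁ − p₂| / (2√(p̄(1 − p̄))), where p̄ is the mean of p₁ and p₂.

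For fixed d, w is largest when the two proportions lie symmetrically about 50%, where w = 2Φ(d/2) − 1.
- d = 0.5: 2Φ(0.25) − 1 = 2 × 0.5987 − 1 = 0.197.
- w = 0.3 requires Φ(d/2) = 0.65, so d = 0.77.

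Even the conversion that ignores dichotomisation, r = d/√(d² + 4) = 0.5/√4.25 = 0.243, falls short of 0.3. It gives N = 134, and power 0.62 at 88.

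**3. Power under d = 0.5.** Noncentrality is N·w², df 1, two-sided α = 0.05. The TAU proportions are assumptions, because the article states none.

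| TAU | iCBT | w | Power, N = 88 | Power, N = 130 | N for 0.8 |
|---|---|---|---|---|---|
| 4.9% | 1.6% | 0.094 | 0.14 | 0.19 | 879 |
| 15.7% | 6.6% | 0.145 | 0.27 | 0.38 | 375 |
| 27.3% | 13.5% | 0.171 | 0.36 | 0.50 | 267 |
| 60% (most favourable) | 40.3% | 0.197 | 0.46 | 0.61 | 201 |

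Worked row: at 15.7%, Φ⁻¹ = −1.007, and Φ(−1.507) = 0.0659. Then p̄ = 0.111 and w = 0.0911 / (2 × 0.315) = 0.145.

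Exact enumeration of the uncorrected χ² test gives 0.09 and 0.16 (4.9%), 0.29 and 0.38 (15.7%), 0.38 and 0.50 (27.3%), and 0.46 and 0.61 (most favourable). The 27.3% is the Background's upper figure for clinically significant post-traumatic symptoms, not for the PTSD diagnosis or for depression; it serves here only to widen the range.

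**4. Ceiling for PTSD at the cited prevalences.** If PTSD vanished under iCBT (p₂ = 0), then w = √(p/(2 − p)).
- 2.4%: 0.110
- 3.1%: 0.125
- 4.9%: 0.158
- 15.7%: 0.292

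Reaching w = 0.3 requires a TAU rate of at least 2 × 0.09 / 1.09 = 16.5%, even with complete elimination.

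**The case against.** - **The number 88 is correct.** A reader might infer a calculation error, or that the 0.8 power is fictitious. Neither is supported: given w = 0.3, power is 0.804. What can be disputed is the assumption.
- **The 0.197 bound is not universal.** It needs a homogeneous, equal-SD normal shift. PTSD by TES also requires criteria A, E and F and separate symptom counts, so it is not one cut of the summed score. Step 2 is directed at women still meeting PTSD criteria, so benefit could concentrate in the upper tail. For example, with 27.3% above the cut under TAU, and only those women improving, by 1.25 SD, the proportion falls to 3.2%. Then w = 0.335 while the overall d is only 0.40. This stands as a limit on the argument, but the plan states no such model.
- **The prevalences are background figures.** The trial enrols women with a low birth rating, an immediate caesarean section or a major haemorrhage, and gives no PTSD rate for them. The highest cited rate, 15.7%, is less than one percentage point below the 16.5% threshold. So w = 0.3 cannot be called impossible in this trial.
- **A w below 0.3 does not itself prove low power at small rates.** Exact power at 88 is 0.93 for 15.7% against 0%. It is 0.80 for 15.7% against 1.2%, the shift implied by the source study's d = 1.25. But the plan deliberately set d = 1.25 aside for d = 0.5.
- **130 is the larger requirement, so 88 may look harmless.** This does not rescue the claim: under d = 0.5, power at 130 is still at most about 0.61.

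A reader might also want a single power figure for EPDS ≥ 12. The article gives no base rate for it, so only the general ceiling applies.

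**Conclusion.** The point holds as an unsupported and internally inconsistent assumption. Under the plan's own d = 0.5 and a uniform normal shift, the binary outcomes have power of at most about 0.46 at 88 and 0.61 at 130. With an assumed 15.7% PTSD under TAU, the values are about 0.27 and 0.38. The ceiling applies to EPDS ≥ 12 as well, and more directly, since that outcome is a simple cut of the summed score. For PTSD the shift model is an approximation, and the true base rate is unknown.

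The conclusion does not extend to the continuous outcomes, whose 130 is sound for d = 0.5. Nor does it show that the proportions must lose their place in the primary hypothesis. Randomisation ended in April 2018, and altering outcome status after that is a separate decision which this calculation does not compel.

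**What to change.** 1. Withdraw the statement that 88 women suffice for the χ² analysis.
2. State assumed TAU and iCBT proportions for PTSD and for EPDS ≥ 12. Use a range, particularly for EPDS, where no base rate is given.
3. Restate power for each proportion at 130 and at the number actually randomised, which the article does not report.
4. Say plainly that the proportions are not powered at 0.8 under d = 0.5.
5. Report them as differences or odds ratios with confidence intervals, so that a null result is not read as no effect.

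The cost is wording in the sample-size section and in the results report. No patients are added and no outcome changes status. The drawback is a less favourable stated power.

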### Procedure

The Care Base Internet Platform including its web-based part (U-CARE eService) was developed within the U-CARE program at Uppsala University. The aim of the U-CARE research program is to prevent and reduce psychosocial malfunctioning in patients and relatives. The U-CARE eService is currently being used for interventions and data collection http://www.u-care.uu.se. The present study is associated with the U-CARE program/eService.

Before discharge from hospital, women rate their overall childbirth experience on a paper and pencil administered Likert-scale (range; 0–10), please see Figure 2. Those with a low rating on the childbirth experience, defined as ≤5 on the Likert scale, and/or exposure to an immediate caesarean section and/or a major bleeding (≥2000 ml) following childbirth (see material section) are asked to consider participation in the study. Immediate caesarean section, is defined as when used for life-threatening situations for either the baby or the mother. About 8 weeks postpartum the women are contacted and informed about the study via telephone. To those interested in participation, information and consent is sent home by mail and to those not responding to contact after three attempts. Partners are also invited to participate at the same time as the mother and they sign the same consent form after reading the information about the study. Participants who consent are provided with login details to the Internet study site. The login and reporting procedures are as follows: Each login requires double authentication. At the first login, participants respond to baseline measures after which they are randomly allocated to either TAU or iCBT+TAU. They are immediately informed about the allocation via an email from the web portal. The partners are allocated together with the mothers. iCBT-1 + TAU and TAU are initiated immediately after randomisation. Participants respond to the questionnaires after iCBT step-1 (at 6 weeks) and after iCBT step-2 (at 14 weeks) followed by measurements annually up to 4 years post treatment. The U-CARE platform automatically sends reminders via email and text messages when measurements are not completed within 14 days. After another 7 days, participants are reminded via a telephone call. Paper copies of the questionnaires will be sent by mail to unresponsive participants. Reminders are also sent to those who delay their initiation of iCBT treatment and when participants delay the weekly treatment modules.

**Fig. 2 Fig2:**
[figure not shown]
JUNO flow diagram. Note. *TAU* treatment as usual; iCBT=internet delivered cognitive behavior therapy *TES* The Traumatic Event Scale, *EPDS* Edinburgh Postnatal Depression Scale, *SWLS* The Satisfaction with Life Scale, *WCQ* The Ways of coping questionnaire, *ENRICH* The communication subscale from the Evaluation and Nurturing Relationship Issues, Communication and Happiness, *RDAS* The Revised Dyadic Adjustment Scale, *PBQ* The Postpartum Bonding Questionnaire, *EQ-5D* EuroQol 5D, *SF-36* Short Form Health Survey – 36, *HADS* Hospital Anxiety and Depression Scale, National register data = The medical birth register, the national patient register, the Swedish prescribed drug register, *QPP* Quality from the patient’s perspective, Health history = Information about previous pregnancies and births are collected at baseline; Obstetric data regarding pregnancy = childbirth, the post partum period and other medical data concerning the current childbirth X^1^ approximately 6-8 weeks after giving birth, this includes assessment of depression (EPDS)

### Randomisation

After completion of the baseline assessment participants are allocated on a 1:1 ratio to either iCBT+TAU or TAU via the U-CARE system. Until randomisation is completed, the researcher is blind regarding the baseline questionnaire-answers. The participants’ allocation is not concealed for any additional caregiver involved and may be disclosed by the participants if they so choose.

### Interventions

#### iCBT step-1 + TAU

The first step of the intervention encompasses iCBT with therapist support at request. Participants can read the material and/or choose to listen to an audio-visual presentation as well as viewing videos covering e.g. breathing retraining and vignettes of childbirth stories. It also includes psychoeducation and basic interventions and techniques that aim to improve health and alleviate symptoms caused by posttraumatic stress and depression [46] (Table 1). The six weekly modules include homework based on the content. The partner receives identical content and a ‘partner instruction’ with specific tasks to perform (support and make room for practice; reflective listening; talk about the birth experience and present symptoms etc.) A psychologist guide, encourage, and respond to questions from the participants. After the completion of each module the psychologist writes an email to the participant to inform her that the week’s CBT is completed. Participants will be informed on a regular basis that they may ask questions or consult the psychologist via email.

**Table 1 Tab1:** Overview of the of the iCBT step-1 week by week for the woman and her partner

	Woman	Partner
Week 1	Information, psychoeducation, breathing retraining	Take part of the material, facilitate, make time, homework reminder
Week 2	Vignettes, common symptoms, fear and avoidance	Discuss the information, remind and encourage practicing
Week 3	Depressive symptoms, significance of relations,“ reflective listening”	Reflective listening, encourage talk about childbirth, remind/encourage practice
Week 4	Exposure, talking about the childbirth	Watch pictures & movies, talk about the experiences, support practice
Week 5	Managing anxiety and depressive symptoms, psychological health, values, recovery	Talk about values, psychological health, and relaxing high demands
Week 6	Summary, repetition and relapse prevention	Talk about the information, make time to summarize, maintenance plan

Note. The content is identical for the partner and the mother except that the partner has additional information with instructions on what to do, discuss, facilitate etc

^1^Every week contains homework assignments based on the content of the module

The women who complete iCBT step-1 and fulfil the criteria for PTSD (according to The Traumatic Event Scale) will be offered iCBT step-2.

#### iCBT step-2 + TAU

The psychological treatment in iCBT step-2 is structured and follows an evidence-based treatment for PTSD [46, 47]. The presentation and the format of the material in step-2 is the same as in step-1. Expressive writing (structured written assignments) is used as an alternative to imagery exposure [48]. iCBT Step-2 is more individualised than iCBT step-1 with weekly therapeutic support via mail. There is no partner content in this step since the empirical evidence is based on an individual treatment protocol (Table 2).

**Table 2 Tab2:** Overview of the of the iCBT step-2

Module	Content
1	Introduction to treatment, psychoeducation
2	Identify & recognize symptoms, breathing retraining (continued through treatment)
3	In vivo-exposure (continued through treatment)
4	Refined in vivo-exposure + intro to expressive writing
5	Expressive writing, imaginal exposure
6	Refined imaginal exposure
7	Finding hot-spots, recovery
8	Summary, maintaining progress, relapse prevention

Note. Every module contains homework assignments based on the content of the module

#### Tau

In all our four study-centres the women rate their overall childbirth experience on a Likert-scale before leaving the hospital. Women who rate their childbirth experience ≤5 are contacted 8 weeks postpartum. All participants in the study are treated according to international guidelines by the local health care system regardless of treatment allocation. TAU includes conventional support according to existing practice at the Department of Obstetrics and Gynaecology in the participating hospitals. TAU can include an opportunity for a follow-up visit with the physician and/or counselling in a fear of birth-unit (often called Aurora clinic) where specially trained midwives and obstetricians work together to help the woman deal with negative experiences from childbirth and with fear of childbirth. Although guidelines exist, the nature of counselling offered differs among hospitals in Sweden [49]. However, the intention in all four study centres is to offer post-partum counselling if needed before the women leave the hospital.

Participants are not prohibited or discouraged from seeking and receiving other care during the study period. If participants signal psychological problems (via email, telephone or questionnaires) they will be contacted and referred to appropriate care.

### Data collection

Participants log in and respond to the questionnaires via the U-CARE web portal at seven time points. The original data are electronically stored on the U-CARE web portal and can only be retrieved by members of the research group. Medical and obstetric data related to the birth will be collected from the patients’ records. A data monitoring committee is not employed; however, suicidal ideation is monitored by the psychologist (see ethical considerations below). The principal investigator (ASS) of the study will restrict access to the final trial data set.

The inclusion of participants for this study started in September 2013. The last day for recruitment of eligible was on the 31st of January 2018 and the last participant was randomised on the 12th of April 2018.

### Measurements

Overall childbirth experience is a paper and pencil administered assessment. The information and instruction are as follows; “We would like to know how you experienced your childbirth. Circle the number between 0 – 10 that best correspond to the overall experience of your childbirth. 0 corresponds to ‘A very bad experience’ and 10 corresponds to ‘A very good experience.’” A low rating, ≤ 5, indicate a negative childbirth experience. For an overview of timing of measurements and data collection please see Table 3.

**Table 3 Tab3:** Timing of measurements and data collection during the JUNO study

	Prenatal	Postnatal	Baseline	Post, 6 weeks	Post, 14 weeks	1 year FU	2 years FU	3 years FU	4 years FU
The mother									
The Medical Birth Register	x	x							
The National Patient Register			x	x	x	x	x	x	x
The Swedish Prescribed Drug Register			x	x	x	x	x	x	x
Overall childbirth experience		x							
Demographics			x						
TES, EPDS^a^			x	x	x	x	x	x	x
SWLS, WCQ, ENRICH, R-DAS, PBQ, EQ-5D, SF-36			x	x	x	x	x	x	x
The partner									
WCQ, PBQ, SWLS, R-DAS, ENRICH, EQ-5D, SF-36			x	x	x	x	x	x	x

Note. Participants are randomized after completion of baseline measures

*TES* The Traumatic Event Scale, *EPDS* Edinburgh Postnatal Depression Scale, *SWLS* The Satisfaction with Life Scale, *WCQ* The Ways of coping questionnaire, *ENRICH* The communication subscale from the Evaluation and Nurturing Relationship Issues, Communication and Happiness, *R-DAS* The Revised Dyadic Adjustment Scale, *PBQ* The Postpartum Bonding Questionnaire, *EQ-5D* EuroQol 5D, *SF-36* Short Form Health Survey–36, *HADS* Hospital Anxiety and Depression Scale

^a^ Primary outcome measures

### Demographics and health history

Demographic data including information about age, level of education, ethnicity and marital status are collected at baseline. Information about previous pregnancies and births are also collected at baseline. Obstetric data regarding pregnancy, childbirth, the postpartum period and other medical data concerning the current childbirth are collected from the patients’ records (see below).

### Primary outcome measures

*The Traumatic Event Scale (TES)* measures post-traumatic stress symptoms related to childbirth, 3 months after delivery [50]. The scale was developed to assess the DSM-IV [8] criteria for PTSD FC. It comprises the stressor criterion A, with the four items formulated as follows; 1) The childbirth was a trying experience, 2) The childbirth was a threat to my physical integrity, 3) During the childbirth I was afraid that I was going to die, 4) During the childbirth I felt anxious/helpless/horrified. The response options for the A criterion are “not at all, somewhat, much, very much”, The A criterion is met if the alternatives “much” or “very much” is chosen on item 1, 2 or 3, and 4. The three categories of PTSD symptoms (in total 17 items) assess re-experiencing (B-criterion), avoidance (C-criterion), and arousal symptoms (D-criterion). The response options for these three categories are “never/ not at all, rarely, sometimes, often” and to be accounted for as presence of a symptom, the alternatives “sometimes” or “often” are required. In accordance with the DSM-IV one of five B items, three of seven C items, and two of five C items are required to fulfil the criteria respectively. The duration criterion (E) is fulfilled if symptoms have been present for 1 month at least. The influence criterion (F) is met if the degree to which it influenced life was ≥ 6 with regard to at least one of the symptoms. The 17 symptom criteria are summed and higher score indicate higher prevalence of symptoms. The symptom scores have shown good internal reliability (*α* = .84) and split half reliability (.90). The difference between the two study arms as concerns the proportion of participants classified as fulfilling the criteria for PTSD at all assessment points will be reported. Means for the summed symptoms score (criteria B, C, and D) will be compared between the study arms. The TES has been adapted for this particular traumatic event (childbirth) where questions point directly at the childbirth [50]. The scale has been developed and evaluated in a Swedish context and thus is considered clinically relevant.

*Edinburgh Postnatal Depression Scale (EPDS)* [51] measures symptoms of depression. It consists of 10 items, rated from 0 to 3, where higher summed scores indicate more symptoms of depression. The summed score ranges between 0 and 30 where a higher score indicate more symptoms. A cut-off point of ≥12 for postpartum depression is often used for screening in clinical settings [52] and is used in this study as well. A population-based study on the Swedish version showed good validity in comparison with a clinical interview [52]. The EPDS is a widely used screening measure of post-natal depression with a sensitivity of 86%, specificity of 78%, high standardised Cronbach’s *α* (.87) and split-half reliability (.88) [51]. Between the two study arms, the difference in the proportion of participants with postpartum depression according to cut-off and means for the summed scores at all assessment points will be reported. EPDS is the most frequently used instrument to screen for post-natal depression and its use will enable comparisons between studies.

